## Abstract

**Introduction:**

More people are living with and beyond a cancer diagnosis. There is limited understanding of the long-term effects of cancer and cancer treatment on quality of life and personal and household finances when compared to people without cancer. In a separate protocol we have proposed to link de-identified data from electronic primary care and hospital records for a large population of cancer survivors and matched controls. In this current protocol, we propose the linkage of Patient Reported Outcomes Measures data to the above data for a subset of this population. The aim of this study is to investigate the full impact of living with and beyond a cancer diagnosis compared to age and gender matched controls. A secondary aim is to test the feasibility of the collection of Patient Reported Outcomes Measures (PROMS) data and the linkage procedures of the PROMs data to electronic health records data.

**Materials and methods:**

This is a cross-sectional study, aiming to recruit participants treated at the Leeds Teaching Hospitals National Health Service Trust. Eligible patients will be cancer survivors at around 5 years post-diagnosis (breast, colorectal and ovarian cancer) and non-cancer patient matched controls attending dermatology out-patient clinics. They will be identified by running a query on the Leeds Teaching Hospitals Trust patient records system. Approximately 6000 patients (2000 cases and 4000 controls) will be invited to participate via post. Participants will be invited to complete PROMs assessing factors such as quality of life and finances, which can be completed on paper or online (surveys includes established instruments, and bespoke instruments (demographics, financial costs). This PROMs data will then be linked to routinely collected de-identified data from patient’s electronic primary care and hospital records.

**Discussion:**

This innovative work aims to create a truly ‘comprehensive patient record’ to provide a broad picture of what happens to cancer patients across their cancer pathway, and the long-term impact of cancer treatment. Comparisons can be made between the cases and controls, to identify the aspects of life that has had the greatest impact following a cancer diagnosis. The feasibility of linking PROMs data to electronic health records can also be assessed. This work can inform future support offered to people living with and beyond a cancer diagnosis, clinical practice, and future research methodologies.

## Introduction

### Cancer survivorship

Improvements in cancer screening, early detection, and treatments mean there are an estimated 2.5 million people living with and beyond cancer in the United Kingdom, which is expected to rise to 4 million by 2030 [1]. Cancer is increasingly viewed as a chronic condition [2, 3], with median overall survival in cancer patients increasing since the 1970s [4]. Though improvements in treatments are reducing mortality and extending life, cancer continues to impact upon people’s lives long after treatment is over. Cancer survivorship refers to the time of diagnosis until the end of life and focuses on aspects of life such as physical, mental, emotional, social, and financial implications that occur from diagnosis, throughout treatment, and beyond [5]. Cancer survivors can face profound and lasting, physical, social, financial and psychological complications secondary to cancer diagnosis and treatment, with an estimated 25% of cancer survivors facing poor health or disability [6, 7].

Cancer survivorship has moved from being marginal to being mainstream on the health agenda [8–10], with survivorship care now perceived as a societal, third sector, and government priority [11]. Aftercare is increasingly provided through risk-stratified pathways, as hospital follow-up is being reduced and more care is being delivered within primary care [8, 10]. A primary care electronic health record (EHR) study reported an increased incidence of chronic illnesses, such as heart failure, coronary artery disease, dementia and diabetes mellitus were identified among survivors of different types of cancers, as compared to matched controls [12]. However, there is currently little evidence concerning: (i) the magnitude and variability between patients in terms of late morbidity, (ii) the costs for primary care, hospitals and patients associated with life after primary cancer treatment, (iii) the cost effectiveness of aftercare services, or (iv) the requirements of users of these services [11].

### Patient Reported Outcome Measures (PROMs)

Healthcare providers strongly focus on the clinical outcomes and tend to give limited consideration to symptom intensity, particularly with subjective symptoms such as fatigue and dyspnoea [13–15]. The importance of capturing the patients’ own perspectives is becoming recognised and incorporated into clinical practice and research [16–18]. PROMs (Patient Reported Outcome Measures) are validated questionnaires completed directly by patients on their health and symptoms. In the UK, the National Health Service (NHS) White Paper, *Equity and Excellence* [19], recommends the wider use of PROMs and patient experience data to place patients at the heart of the health service. PROMs studies have revealed the significant unmet needs of cancer survivors, for example: for breast cancer, studies have shown deficits in physical and social functioning, arm and/or shoulder pain, fatigue, sexual difficulties, insomnia and financial issues [20–25]; for colorectal cancer survivors, studies have indicated bowel and/or urinary control issues, constipation, diarrhoea, sexual difficulties, fatigue, pain [26–28]; and within ovarian cancer, sexual dysfunction and psychosocial issues such as distress depression and anxiety [29–31].

Conversely, some studies have found that for certain cancers, survivors score similarly to the general population for some aspects of quality of life [22, 28, 31–33]. However, there remains a lack of high-quality large-scale studies comparing the quality of life (QoL) for long-term cancer survivors with age and gender matched controls and larger sample sizes. The department of Health recommended the introduction of an innovative quality of life metric to track and respond to the long-term impact of cancer. The Independent Cancer Taskforce in their strategy for England 2015–2020 [9] and NHS Long Term Plan [34] have recommended the introduction and implementation of Quality of Life data collection for cancer survivors in England. Pilot projects are underway looking at electronic methods of patient self-reported questionnaires. Therefore, this paper proposes a protocol to test the feasibility of integrating PROMs data into NHS systems in order to link with PROMs and healthcare records, and to gain a broader picture of life following a cancer diagnosis compared to matched controls.

### Comprehensive Patient Records (CPR)

The study outlined in this paper is part of a larger programme of work called C*omprehensive Patient Records for Cancer Outcomes* (known as CPR) [35, 36]. CPR aims to develop a clearer picture of what happens to people living with and beyond cancer, and the costs to individuals and the healthcare system associated with their care, by securely linking de-identified information from patient questionnaires, electronic primary care and hospital records. The analysis is based upon data drawn from the records of 100,000 cancer patients and 500,000 matched controls. The CPR study comprises five workstreams: (1) data linkage, (2) co-morbidity and late effects of cancer, (3) identifying and predicting recurrence, (4) a health economic analysis of the long term costs of cancer to individuals and the healthcare system, and (5) patient reported costs of living with and beyond cancer (known as the Patient Reported Outcome Measures (PROMs) workstream). The PROMs workstream is the focus of this paper.

CPR PROMs involves collecting PROMs data directly from a subset of the main study population, and integrating it with an identical duplicate of the data collected from Electronic Health Records (EHR) in the main CPR study for this subset of patients. In doing so, CPR PROMs will test the feasibility of collecting PROMs from patients, and linking the PROMs data to patient records. This will enable a truly ‘comprehensive patient record’ to provide a broad picture of what happens to cancer patients across their cancer pathway, and the long-term impact of cancer treatment. Comparisons can be made between the cases and controls, to identify the aspects of life that has had the greatest impact following a cancer diagnosis.

### Aim

The primary aim of this CPR PROMs study is to examine the long-term QoL, personal finances, psychological health, physical health, and social impacts of people living with and beyond a cancer diagnosis. The secondary aim of the study is to test the feasibility of the collection of PROMs data and the linkage procedures of the PROMs data to routine data, to investigate the full impact of cancer on individuals across a wide range of domains. Linkage of the PROMs data to routine data could enable a truly ‘comprehensive patient record’ to be created showing the long-term effects of cancer on factors such as quality of life, health, co-morbidities, and well-being.

### Objectives

To collect PROMs data from a cohort of cancer survivors in breast, colorectal and ovarian cancer, and compare these with PROMs data collected from matched individuals without cancer. Data will include: long-term QoL, personal finances, psychological, and social impacts.To integrate PROMs data with de-identified routinely collected primary care and hospital records data using the secure systems for data linkage approved for our wider programme of work [35, 36].To test the feasibility of the PROMs collection and data linkage procedures for use in other research studies and patient care.

An overview of the data collection procedures and pseudonymisation is displayed in Fig 1.

**Fig 1 pone.0266804.g001:**
[figure not shown]
Diagram illustrating a brief over view of CPR PROMs data collection and pseudonymisation. *Note*. PPM (Patient Pathway Management) is an electronic patient record to record and deliver patient records across the Leeds Teaching Hospital Trust NHS Spine supports the IT infrastructure for health and social care in England and enables information to be exchanged across local and national computer systems Clinical Research Facility conducts early stage and experimental trials in a range of disease specialities.

## Materials and methods

### Study design

The study uses a cross-section of matched-control PROMs survey with data linkage to de-identified hospital data (via Leeds Teaching Hospitals NHS Trust, LTHT) and primary care (via The Phoenix Partnership, TPP).

### Study setting

Patients will be recruited from LTHT, one of the largest teaching hospitals in Europe. The hospital provides local and specialist services for the immediate population of 770,000 and regional specialist cancer care for up to 5.4 million people. TPP provide ResearchOne as a primary care research database containing de-identified data extracted from consenting SystmOne GP practices. Some primary care practices using SystmOne have agreed for their practice data to be included in a de-identified format on ResearchOne (a health and care research database which contains linked data from primary and secondary health care), which is also provided by TPP. Full details of the health records linkage is provided in the protocol for our wider programme of work [35, 36].

### Participants

Patients will be eligible for this study if they are registered on the LTHT electronic patient record and listed as using a Leeds Clinical Commissioning Group primary care practice. Specific inclusion and exclusion criteria for the cases and matched controls are specified below.

### Inclusion criteria for cancer cohort

A diagnosis of colorectal cancer (ICD-10 C18—C20), breast cancer (ICD-10 C50) or ovarian cancer (ICD-10 C56)Approximately five years beyond their first cancer diagnosis (e.g., index date = 2013 ± 4 years). Date. Index date was the patient’s clinic appointment date. The year band is expanded incrementally until the full cancer cohort is obtained.18–100 years old on date of diagnosis

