### Inclusion criteria for control cohort

Reviewed by LTHT dermatology services on a two week wait for potential skin cancer, but were not diagnosed with cancerNo cancer diagnosis recorded within LTHT records at any time.One dermatology appointment within 12 month of the matched case’s cancer diagnosis (their index date).Age 18–100 on appointment date.No further dermatology appointment in the 12 months following their index date.Could be matched to cases by age, sex and primary care practice.

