#### Quality of Life in Adult Cancer Survivors (QLACS)

QLACS is a 47-item measure of QoL amongst adult survivors of cancer at least five years post diagnosis [45]. The instrument comprises of cancer specific scales and generic scales. The generic scales do not mention cancer and thus make the instrument an appropriate measure to make comparisons between cancer and non-cancer populations [58]. QLACS was highlighted in the 2010 National Cancer Survivor Initiative ‘Vision’ document [17], and has been previously used with breast, colorectal and gynaecological cancer patients [45, 58, 59]. For the cancer specific domains items with the term “cancer” or “cancer treatment” are changed to “health” or “healthcare treatment” within the control group questionnaire. Two subscales are not included in the control group survey as they are deemed as not appropriate: the ‘Benefits of cancer’ and ‘Distress over recurrence”.

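### The case window of 2013 ± 4 years does not match a population around five years after diagnosis, includes people outside the stated QLACS population, and rests on an unclear index date

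*Protocol article*

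**What the plan says.** The abstract (Materials and methods) describes the cases as "cancer survivors at around 5 years post-diagnosis", and the Feasibility assessment section also refers to recruiting people five years on from diagnosis. The operational rule, under Inclusion criteria for cancer cohort, is "Approximately five years beyond their first cancer diagnosis (e.g., index date = 2013 ± 4 years". It continues: "The year band is expanded incrementally until the full cancer cohort is obtained". No maximum width and no minimum time since diagnosis is stated.

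The same criterion says "Index date was the patient’s clinic appointment date". The control criteria require "One dermatology appointment within 12 month of the matched case’s cancer diagnosis (their index date".

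The Primary outcome section makes the QLACS primary, compares its generic summary scores between cases and matched controls, and names subgroups by cancer type only. The QLACS section states: "QLACS is a 47-item measure of QoL amongst adult survivors of cancer at least five years post diagnosis".

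**The concern.** The eligibility rule decides whose experience the primary comparison describes. A window four years either side of a five-year target can bring in people soon after treatment alongside people a decade on, while the article presents them as one group around five years out. Some would also fall short of the duration that the article itself attaches to its primary instrument.

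The survey appears to have been built for a five-year cohort. Under Section 1: Questions about you, cases are asked about their relationship status at diagnosis, and controls about theirs 5 years ago. These recall periods line up only if cases are close to five years from diagnosis.

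The index date adds a second difficulty. If the band is applied to a clinic appointment, it does not by itself control time since diagnosis, and whoever builds the search query cannot tell from the text which date governs.

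**Working it through.** **Inputs**
- Window: 2013 ± 4 years, so 2013 − 4 = 2009 to 2013 + 4 = 2017 (Inclusion criteria for cancer cohort).
- Earliest plausible mailing: the HRA approval, 4 October 2018 (Compliance and approvals). The mail-out date is not stated, so mailing from then to the end of 2019 is an assumption.
- The index date is treated as the diagnosis date, since the criterion uses it to define time beyond first diagnosis. If a case's appointment came after diagnosis, the true times are longer.

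**Reproducing the plan's figure.** Time since diagnosis = survey year − index year. At the centre, 2018 − 2013 = 5, which agrees with the stated five years and suggests a survey planned for about 2018.

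**Range at ±4.** Index dates run from 1 January 2009 to 31 December 2017. The share under five years is the part of the window later than the survey date minus five years, divided by the nine-year window.

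| Survey date | Shortest (years) | Longest (years) | Share of calendar window under 5 years |
|---|---|---|---|
| 4 Oct 2018 | 0.76 | 9.75 | 47% |
| 31 Dec 2018 | 1.00 | 10.00 | 4/9 = 44% |
| 1 Jul 2019 | 1.50 | 10.49 | 3.5/9 = 39% |
| 31 Dec 2019 | 2.00 | 11.00 | 3/9 = 33% |

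A case diagnosed on 31 December 2017 reaches five years on 31 December 2022, so at ±4 any earlier mailing includes someone under five years.

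**Narrower and wider bands.** In whole years for a 2018 survey, ±1 gives 4 to 6, ±2 gives 3 to 7, ±3 gives 2 to 8, ±4 gives 1 to 9 and ±5 gives 0 to 10. The shares of the calendar window under five years are:

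| Band | Survey 31 Dec 2018 | Survey 31 Dec 2019 |
|---|---|---|
| ±1 | 1/3 = 33% | 0/3 = 0% |
| ±2 | 2/5 = 40% | 1/5 = 20% |
| ±3 | 3/7 = 43% | 2/7 = 29% |
| ±4 | 4/9 = 44% | 3/9 = 33% |

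The result therefore depends on both the band reached and the mailing date, and the article fixes neither. As no cap is stated, ±4 is not a guaranteed limit.

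**Index date.** The case criteria name the clinic appointment. In the control criteria the words "cancer diagnosis (their index date" put the term directly after the matched case's diagnosis, and 'their' could mean the case or the control. A later control criterion counts 12 months without a further dermatology appointment from the same term, which makes sense only for the control. So the term could denote a case's clinic appointment, a case's diagnosis or a control's dermatology appointment.

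**The case against.** The strongest reply has four parts.

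- **The five-year floor belongs to the instrument's description.** It is not an eligibility rule. The article asks for cases around five years out, never at least five. The main comparison uses generic scales that the article says do not mention cancer and suit comparison with people without it, and controls, who have no diagnosis date, complete them too. This stands. A reader might infer that cases under five years make the primary comparison invalid; the document does not support that.
- **The band is an example and is widened in steps.** Expansion may stop before ±4, and the mailing date is unknown. This also stands, and it is why the size is given as a range. It does not remove the conflict, because the rule permits ±4 and sets no limit.
- **No direction of bias is established.** A reader might expect recent cases to enlarge the case-control difference. Nothing in the document shows this, and controls are tied in calendar time to the matched case's diagnosis. What is affected is whom the result describes.
- **Analysis by time since diagnosis may be in a statistical analysis plan that is not shown.** That is possible, so its absence from the article is not the fault raised here. The fault is a stated rule that does not fit the stated population.

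The index-date wording may be partly garbled text, and the reference to first diagnosis in the same criterion shows what was intended. It still needs correcting, because the search query is built from these criteria.

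**Conclusion.** The point holds as an inconsistency in who counts as a case. Under the assumption of mailing between October 2018 and the end of 2019, the ±4 window spans about 1 to 2 years at the near end and about 10 to 11 at the far end, with 33% to 47% of the calendar window under five years. That is wider than 'around five years' can reasonably cover, and it includes people outside the population for which the article describes its primary measure.

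The percentages should not be read as shares of patients. That would need an even spread of cases over the years and full expansion to ±4, and the document gives neither. The finding does not show that QLACS scores are unusable under five years, or that the contrast is biased in a known direction. It shows that a contrast of mixed durations could be presented as one around five years after diagnosis.

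**What to change.** 1. Define the case index date as the date of first diagnosis of the qualifying cancer, and the control index date as the dermatology appointment. Use the terms consistently in both sets of criteria.
2. Compute time since diagnosis at survey for every case.
3. State a cap on the band that is consistent with 'around five years', or else describe the population throughout as the range actually admitted.
4. Report the QLACS generic-score comparison by time since diagnosis, and prespecify an analysis restricted to cases at least five years out with their matched controls.

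Widening the band backwards only is an option, not a requirement. It would keep cases at or beyond about five years, but it moves the cohort further from five years on average, increases selection on survival and may not fill the cohort.

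The cost is a rewording of the eligibility criteria, a change to the query if mailing has not begun, and a little more analysis. The restricted analysis will be less precise because it uses fewer cases. If mailing is already done, steps 2 and 4 and the description in step 3 remain possible.

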### Inclusion criteria for control cohort

Reviewed by LTHT dermatology services on a two week wait for potential skin cancer, but were not diagnosed with cancerNo cancer diagnosis recorded within LTHT records at any time.One dermatology appointment within 12 month of the matched case’s cancer diagnosis (their index date).Age 18–100 on appointment date.No further dermatology appointment in the 12 months following their index date.Could be matched to cases by age, sex and primary care practice.

### Sample size

The survey will be sent out to around 6,000 potential respondents. The estimated consent rate for cases is around 60% which is based on similar postal PROMs surveys recruitment rates of: 63% [37], 68% [38], 49.1% [39]. The anticipated consent rate for controls is lower and estimated at between 23.9% [39] and 30% based on recent returns from a control study matched to cases of men with prostate cancer [40]. Based on expected consent rates, this should result in a sample size of around 1,000 to 1,200 in each group (cases, controls). A power sample size calculation was undertaken using the study’s main measure the QLACS (Quality of Life in Adult Cancer Survivors), and this number exceeds the number of respondents required for 90% power for all the data analysis subsets.

#### Matching process

Cancer cases to control cases will be at a ratio of one to two (2,000 controls and 4,000 cases).

Match the cancer case (2:1 ratio of controls to cancer cases)

Sex.By primary care practice.Age: date of birth is within (+/-) 30 months. The time band is expanded incrementally until the PROMs cancer cohort has two matches. If an expansion of the band is necessary, the matching process will be re-run for the whole PROMs cohort to avoid bias from some cases being closer matched than others (other than at random).

